### Phase 2: Examining the Relationship Between Postural Responses and Acute Lower Extremity Musculoskeletal Injuries

#### Participants

For phase 2, a minimum of 200 subjects will be recruited before the start of their competitive season and prospectively tracked for 1 year. All subjects will be between the ages of 18 and 30 years and tested on site in the Athletic Training Clinics at the University of Utah. Informed written consent will be obtained from all participants.

#### Inclusion and Exclusion Criteria

For phase 2, inclusion criteria are as follows: (1) age 18 to 30 years and (2) current participant in NCAA Division I athletics. Exclusion criteria are as follows: (1) recent (within 6 months) or planned surgery that would result in future time loss and practice/competition exposure and (2) chronic conditions that could confound testing procedures (overuse injuries, medical conditions).

#### Assessment Procedures

Phase 2 assessments will be included as part of preseason physical baseline testing. Acute lower extremity musculoskeletal injuries for each athlete in phase 2 will be prospectively tracked for 1 year from the date of first team activity.

The phase 2 assessment will be identical to the phase 1 matched control athlete assessment. Additionally, mTBI history will be recorded using the Ohio State Traumatic Brain Injury Identification Method (OSU TBI-ID). While the OSU TBI-ID is not made specifically for mTBI, it is well validated (Corrigan and Bogner, 2007; Bogner and Corrigan, 2009) and recommended by the National Institute of Neurological Disorders and Stroke as a Common Data Element for mTBI studies. Lower extremity injury history, including the date of injury, location, type of injury (e.g., sprain, fracture), cause, time lost from sport, and relation of each injury to the athlete's primary sport, will be recorded.

#### Prospective Musculoskeletal Injury Risk

Acute lower extremity musculoskeletal injuries for each athlete in phase 2 will be prospectively tracked for 1 year from the date of their first team activity. Injury data will be queried from the athletes' electronic medical records documented by the University of Utah Athletic Training Staff and maintained for the Pac-12 Sports Injury Registry Management and Analytics Program. Injuries of interest will include any acute orthopedic injury of the lower extremity, pelvis, lumbar spine, or abdomen that resulted in time lost, including but not limited to joint sprains, musculotendinous strains, and fractures. Because abdominal and lumbar muscles are required for stability and movement control (Cholewicki et al., 1997), and the lumbar spine is a critical junction of postural control during sport with high musculoskeletal loads and compressive muscle forces, both lumbar spine and abdominal injuries will be included. Any injury that results in an athlete being unable to fully participate in training or match play will be considered a time loss injury (Fuller et al., 2007; Howell et al., 2018a). Overuse injuries and preexisting conditions will be excluded. The primary outcome measure will be time to first musculoskeletal injury. The number of injuries within 1 year and severity of injuries (time lost from a given injury) will be included as secondary outcomes.

#### Statistical Analysis

Time from first team activity to first musculoskeletal injury will be summarized using Kaplan–Meier methods. Cox proportional hazards models will be constructed to determine if time to stabilization during postural responses is associated with faster times to injury in the general collegiate athlete population (hypothesis 3a). Similar models will be performed for each secondary outcome. Models will first be unadjusted and then potentially adjusted for age, gender, sport, history of a recent musculoskeletal injury, and history of mTBI before enrollment. The number of variables that we will adjust for will depend on the number of musculoskeletal injuries observed. The inclusion of sport as a covariate will account for variation in the biomechanical demands, exposures, and schedules across different sports. To determine if time to stabilization is a better predictor of future injury than clinical score, similar models will be constructed for the P&R clinical score, and we will assess each model's predictive ability using c-statistics (hypothesis 3b). Models with the highest c-statistic value will indicate the outcome most predictive of time to injury.

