Similar to static balance and gait, clinical assessments of reactive postural responses in other populations rely on scoring guidelines based on visual observation, but wireless, wearable inertial sensors can improve the accuracy of these assessments. For example, inertial sensors can detect differences in reactive postural responses between disease states [healthy control, multiple sclerosis (Smith et al., 2016; El-Gohary et al., 2017), Parkinson disease (Smith et al., 2016)]. Wearable sensors also provide information about quality of movement using a variety of objective characteristics. However, no study has used inertial sensors to quantify reactive postural responses in clinical mTBI settings. Improved understanding of how mTBI impacts the quality of balance recovery is critical to determine the implications of persistent balance impairments after mTBI, such as increased injury risk, and to develop clinical rehabilitation strategies to optimize athletes' neuromuscular control prior to return to competitive activity.

Our central hypothesis is that the high rate of musculoskeletal injuries after mTBI is in part due to impaired postural responses and balance recovery. Therefore, the purpose of this study is to (1) characterize reactive postural responses in athletes with recent mTBI compared to healthy control subjects, (2) determine the extent to which postural responses remain impaired in athletes with recent mTBI who have been cleared to RTP, and (3) determine the relationship between postural responses and acute lower extremity musculoskeletal injuries in a general sample of healthy collegiate athletes. We hypothesize that (1a) athletes with recent mTBI will take longer to regain balance during assessments of reactive postural responses compared to control athletes; (1b) athletes with recent mTBI will have larger deficits, in postural responses when simultaneously performing a dual task, relative to single task; (2) athletes with recent mTBI will improve reactive postural responses but will still demonstrate deficits compared to control subjects at all time points; (3a) that impaired postural responses at a baseline assessment will be associated with a faster time to acute musculoskeletal injury in healthy collegiate athletes; and (3b) objective measures of reactive postural responses will be better predictors of musculoskeletal injuries compared to clinical measures.

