##### Clinical reaction time

At every time point, both athletes with mTBI and matched control athletes will perform the Clinical Reaction Time test (RT_clin_). RT_clin_ is a clinical test measuring simple reaction time using an 80-cm dowel with one end inserted in the middle of a hockey puck (Eckner et al., 2010). The participants will sit with their dominant arm on a table, leaving their wrist and hand off the side of the table. The investigator then brings the hockey puck to the level of the athlete's first finger and thumb. After a random duration between 2 and 5 s, the investigator releases the dowel, and the participant attempts to catch the dowel as soon as possible. The distance from the superior aspect of the hockey puck to the superior aspect of the participant's hand is measured. For the present study, two practice trials followed by eight measured trials will be completed by athletes at each assessment.

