Reactive postural responses are common in athletic competition and essential for athlete safety, but this domain of balance control has not been studied extensively after mTBI. Time to stability after dynamic movement can discriminate between those with history of mTBI and healthy controls (Lynall et al., 2020), suggesting that stability may be an important post-mTBI measure. However, no study has examined reactive postural responses in athletes with mTBI. We suspect the lack of knowledge concerning reactive postural responses after mTBI stems from two sources. First, reactive postural responses have been historically considered reflexive (subcortical) (Jacobs and Horak, 2007; Jacobs, 2014). However, it is likely that reactive postural responses rely on interaction among spinal circuits, the brainstem, and the cortex (Jacobs and Horak, 2007). As the focus of mTBI has traditionally been on cortical damage, postural responses may have been considered too automatic/reflexive to be disrupted by mTBI. The second possible reason for a gap in knowledge is logistical; traditional assessments of postural responses require sophisticated moving platforms (Zettel et al., 2008a,b) or tether-release (MacKey and Robinovitch, 2005; Inness et al., 2015) setups. Given some of the patient burden hurdles ingrained within clinical mTBI research, it is perhaps unsurprising that few studies have examined postural responses using these types of equipment. In fact, in designing this protocol, we considered implementing similarly controlled postural response paradigms (e.g., tether-release, moving platform, etc.). However, the need for a clinically feasible testing paradigm was critical to minimize the burden on student-athlete participants. Therefore, we selected the P&R test, a clinical test traditionally quantified using visual scoring. The notable weakness of this task is the relative simplicity for highly athletic individuals—few athletes should take multiple steps or struggle to recover. The use of wearable sensors is therefore essential and enables quantitative metrics of response latency, step length, and time to stabilization. The combination of wearable inertial sensors with the clinical P&R test facilitates assessments of reactive postural responses within an athletic training room with minimal added burden on the athlete. If we find athletes with recent mTBI take longer to regain stability or exhibit longer step latencies, it will provide evidence that mTBI impairs the reactive restoration of balance, demonstrating that mTBI affects all domains of balance control. Additionally, if we find differences between groups across time, it will support our hypothesis that postural responses are persistently impaired after mTBI. Such findings, coupled with the clinical feasibility of the P&R assessment, may spur the integration of postural response testing into the clinical management for mTBI. In the future, more work will be needed to develop outcome measures with established cutoff values for return-to-to play that could be incorporated into a testing battery.

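### Hypothesis 3b is stated against clinical measures in general, but its only planned comparator is the three-level Push and Release step score

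*Protocol article*

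**What the plan says.** The last paragraph of the Introduction states hypothesis 3b as "objective measures of reactive postural responses will be better predictors of musculoskeletal injuries compared to clinical measures". Nothing there limits which clinical measures are meant.

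The phase 2 Statistical Analysis section gives the test of 3b. Cox models are fitted for time to stabilization, and "similar models will be constructed for the P&R clinical score". The decision rule is "Models with the highest c-statistic value will indicate the outcome most predictive of time to injury".

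The Outcome Measures section defines the P&R clinical score on three levels: 0 for a fall, 1 for unaided recovery in several steps, 2 for recovery in a single step. The Discussion describes the task as relatively simple for this population and expects that "few athletes should take multiple steps or struggle to recover".

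The phase 2 battery is broader than the P&R test: "The phase 2 assessment will be identical to the phase 1 matched control athlete assessment". That assessment includes reaction time, since "both athletes with mTBI and matched control athletes will perform the Clinical Reaction Time test" at each visit, with eight measured trials. It also includes the BESS, with errors counted over the first 20 s of each trial.

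**The concern.** The hypothesis and its analysis differ in scope. The hypothesis is about clinical measures as a class; the analysis uses one of them, and it is the one the authors themselves expect to separate athletes poorly. Two other clinical measures are recorded in the same athletes and are left out.

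What is at stake is the conclusion. If time to stabilization has the higher c-statistic, the natural report is that 3b is confirmed. Readers would then take it that sensors beat the tests an athletic department already uses. The comparison would not have examined those tests.

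**Working it through.** **Does any other phase 2 text bring the omitted tests in?** The section also says "Similar models will be performed for each secondary outcome". The P&R secondary outcomes listed under Outcome Measures are step latency, step length and the clinical score. The phase 2 secondary outcomes are the number and severity of injuries. BESS errors and clinical reaction time are in neither list, so this sentence does not cover them.

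**Does the article treat them as clinical tests relevant to injury?** Yes. The Introduction names BESS and clinical reaction time among several clinical tests that were examined as predictors of musculoskeletal injury after mTBI.

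**The plan's own figure.** Inputs from Sample Size Justification: N = 200, event rate 22%, SD 1 s, alpha 0.05 (taken as two-sided), power 80%.
- Events: 0.22 × 200 = 44.
- Minimum hazard ratio: exp[(1.960 + 0.842)/(1 × √44)] = exp(2.802/6.633) = 1.526, which rounds to the stated 1.53.
- Power at 1.53: Φ(6.633 × ln 1.53 − 1.960) = Φ(0.861) = 80.5%.

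The figure reproduces and is not in question.

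**How much could a ceiling matter?** The article does not give the share of athletes scoring below 2, so shares of 5% to 30% are assumed. Harrell's c was simulated with exponential times, censoring at 1 year and 22% events overall. The score was treated as below ceiling or not.

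| Predictor | c-statistic |
|---|---|
| Continuous, HR 1.53 per SD (design value) | 0.62 |
| Continuous, HR 1.2 per SD (assumed) | 0.55 |
| Score, 5% below ceiling, HR 2 / HR 3 (assumed) | 0.52 / 0.54 |
| Score, 10% below ceiling, HR 2 / HR 3 | 0.54 / 0.56 to 0.57 |
| Score, 20% below ceiling, HR 2 / HR 3 | 0.57 / 0.60 |
| Score, 30% below ceiling, HR 2 / HR 3 | 0.58 / 0.62 |

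A score that few athletes fall below has a c-statistic close to 0.5 even when those few carry a clearly raised hazard. As the share below ceiling grows, the handicap shrinks.

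A second simulation took the score to be stabilization time cut at a threshold, with N = 200 and HR 1.53 per SD. With 5%, 10% and 20% below ceiling, the continuous measure had the higher c-statistic in about 99%, 99% and 95% of studies (mean c 0.61 to 0.62, against 0.53, 0.54 and 0.56). In that setting the ranking is expected, because the score is a coarser version of the same quantity. It carries no information about BESS or reaction time.

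**The case against.** The strongest reply is that the analysis section already puts the question narrowly, for the step score alone: "To determine if time to stabilization is a better predictor of future injury than clinical score, similar models will be constructed for the P&R clinical". Comparing sensor-based and visual scoring of the same task is a coherent like-for-like design that isolates the value of instrumentation. BESS and reaction time would also change the construct being measured. Shortly before 3b, the Introduction says that clinical assessments of reactive responses rely on visual scoring, which gives the narrow reading some support. This stands as a defence of the analysis, but not of the hypothesis wording, which is plural and unrestricted. A fuller analysis plan might add comparators, but the article itself names the 3b comparator.

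Three stronger readings are tempting, and the article does not support them.

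- *The trial cannot answer 3b at all, because the score cannot rank athletes.* The narrow question is answerable. The article expects few multiple-step recoveries, not none, and the phase 1 analysis treats a high ceiling as conditional. The test is done with eyes closed, in four directions, under single and dual task: at least eight conditions. If 5% of trials fell below the top score independently (assumed), 1 − 0.95^8 = 34% of athletes would have at least one such trial. How scores are combined is not stated.
- *A weak sensor measure would always outrank a score that marks a high-risk group.* With 10% below ceiling and HR 3, the score reaches 0.56 to 0.57 against 0.55 for a sensor measure at HR 1.2 per SD. Several other gaps are only about 0.01, with 44 events expected.
- *BESS or reaction time would reverse the result.* A measure with HR 1.3 per SD would have c of about 0.58, but nothing in the article supports that hazard ratio. The Introduction reports that both tests failed to predict injury after mTBI. That evidence concerns athletes after mTBI rather than the general healthy sample of phase 2, so it does not settle the matter either way.

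**Conclusion.** The mismatch is real and does not depend on the ceiling. The analysis labelled 3b can establish only whether time to stabilization predicts injury better than the P&R clinical score; it cannot support the broader claim about clinical measures.

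The expected ceiling adds a caution: under a highest-c-statistic rule, a win over a score with little spread may largely reflect that lack of spread. Its size is uncertain. Across the assumed shares of 5% to 30% below ceiling at HR 2, the score's c-statistic runs from about 0.52 to 0.58, against about 0.62 for time to stabilization at the design effect. The shares and the score's hazard ratios are assumptions; only the 22% event rate and HR 1.53 come from the article.

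This should be corrected because 3b is a named hypothesis. The analysis of 3a and its sample size are untouched.

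**What to change.** In the phase 2 Statistical Analysis section, add BESS total error count (first 20 s) and mean clinical reaction time as 3b comparators, in the same Cox and c-statistic form as the P&R clinical score. Claim 3b for clinical measures only if time to stabilization outperforms these as well. Otherwise, word both hypothesis 3b and its conclusion as better than the P&R clinical score. Settle this before the injury data are analysed, so that the choice of comparators is not post hoc.

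The cost is two further models on data already being collected, or one sentence of rewording. The drawback of the first option is that 3b becomes harder to confirm.

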**Figure 2 F2:**
[figure not shown]
(Left) Support was released at time 0 (solid yellow). Step latency (blue dashed line) and time to stabilization (yellow dashed line) are marked.

Using data from the sensor on the investigator's hand, release of support (*t*_0_) will be identified when acceleration is >5% of gravity. Step latency will be calculated as the amount of time (seconds) from *t*_0_ to first foot movement. First foot movement will be detected when foot acceleration >7% of gravity and rotational rate is >7 degrees/s (El-Gohary et al., 2017). To determine step length (meters) of the first step, the double integral of acceleration of the foot from first foot movement to the next zero velocity instant will be calculated. Magnitude thresholds of 97.4 degrees/s for rotational rate and 0.8 m/s^2^ relative to gravity for acceleration will be used to determine the zero velocity instant (Rebula et al., 2013). Time to stabilization will be calculated as the amount of time (seconds) from *t*_0_ to stabilization. Stabilization will be detected when lumbar acceleration <7% of gravity and rotational rate <7 degrees/s, after the last step (El-Gohary et al., 2017).

The primary outcome measure will be time to stabilization. Secondary outcomes include step latency, step length, and the clinical score (number of steps) (Horak et al., 2009). The clinical score will be rated as follows: 0 = fall, 1 = recovers independently but takes more than 1 step, 2 = recovers independently with one step.

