#### Statistical Analysis

Aim 1 of phase 1: *t* tests will be used to determine if time to stabilization during the P&R differs between healthy subjects and subjects <48 h after concussion. Linear regression models will assess group differences while controlling for potential confounders of age, sex, contact/noncontact sport, and BMI. Concussion history will be recorded and explored as a covariate if necessary. As clinical scores are ordered with three levels, Wilcoxon Mann-Whitney *U* tests and generalized linear models for ordered multinomial outcomes (ordinal logistic regression) will compare clinical scores between groups. If the clinical scores exhibit a high ceiling effect, scores will be dichotomized and analyzed using χ^2^ tests and logistic models. *t* tests will assess whether concussed athletes had greater differences between single- and dual-task conditions relative to controls.

Aim 2 of phase 1: Bonferroni-adjusted *t* tests will be used to compare groups PostRTP to determine whether athletes with a recent mTBI take longer to stabilize during reactive postural responses after being medically cleared to RTP. Analogous secondary tests will be used for the PreRTP and 6Month assessments. We will also compute the difference in time to stabilization between assessments (e.g., change from Acute to PostRTP) to determine whether concussed athletes improved their postural responses over time. *t* tests will compare the group differences in the change between assessments. Longitudinal analysis using generalized estimating equations (GEEs) with compound symmetry working covariance models will be used to contrast each outcome of the P&R test at each assessment while controlling for lean direction; single vs. dual task; and possible confounders of age, sex, contact/noncontact sport, and BMI. A group-by-assessment interaction will determine if adjusted group differences changed between assessments. Two- and three-way interactions with task (group × task, group × task × assessment) will be included to test for group-difference in task, and if significant, final models will include these interactions. Ordinal logistic regression in a GEE framework will be used to assess changes in clinical scores between assessments.

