#### Sample Size Justification

We will have 80% power to detect a minimum hazard ratio of 1.53 per 1-s increase in stabilization time with a total sample size of 200 healthy participants, an event rate of 22%, and a standard deviation of 1 s using a Cox regression model at the 0.05 significance level. The event rate was estimated from the average number of athletes who experienced musculoskeletal injuries at the University of Utah from 2015 to 2018.

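### Hypothesis 3b is decided by whichever same-sample c-statistic is higher, so the claim that the sensor measure predicts injury better has no error control

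*Protocol article*

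**What the plan says.** The Introduction states hypothesis 3b as a superiority claim: "objective measures of reactive postural responses will be better predictors of musculoskeletal injuries compared to clinical measures". The phase 2 Statistical Analysis section turns this into a comparison of Cox models. One set uses time to stabilization; then "similar models will be constructed for the P&R clinical score, and we will assess each model's predictive ability using c-statistics (hypothesis 3b"). The deciding sentence is "Models with the highest c-statistic value will indicate the outcome most predictive of time to injury".

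The comparator is an ordered score with three levels, defined under Outcome Measures: "0 = fall, 1 = recovers independently but takes more than 1 step, 2 = recovers independently with one step". The Discussion expects it to discriminate poorly in this population: "few athletes should take multiple steps or struggle to recover". The phase 1 Statistical Analysis section provides for this ("If the clinical scores exhibit a high ceiling effect, scores will be dichotomized"), but the phase 2 section does not carry the provision into the c-statistic comparison.

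The phase 2 Sample Size Justification covers the hazard ratio for time to stabilization, which is hypothesis 3a. It gives no figure for 3b. The article attaches no interval, test or validation to the c-statistic comparison.

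**The concern.** A c-statistic estimated from about 44 events is imprecise, and so is the difference between two of them. A rule that credits the larger value, whatever the gap, always returns a winner and cannot return the answer that the data do not distinguish the two measures. The stated conclusion would be that a sensor measure predicts injury better than clinical scoring, and a reader could not tell that conclusion from chance.

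Two features may make it worse. Both c-statistics come from the athletes used to fit the models. A fitted model that is free to choose the sign of its coefficient tends to show a c above 0.5 even for noise, and this upward drift is larger for a continuous predictor than for a heavily tied score.

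There is also a mismatch of scope. The hypothesis speaks of clinical measures in the plural, but the analysis for 3b names only the Push and Release clinical score. Table 1 lists the BESS and clinical reaction time for both groups at all time points, and phase 2 Assessment Procedures makes its assessment the same as that of the phase 1 controls. Both tests are therefore collected in phase 2.

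**Working it through.** **Inputs from the protocol (phase 2 Sample Size Justification).** "a total sample size of 200 healthy participants", event rate 22%, SD of time to stabilization 1 s, hazard ratio 1.53 per 1 s, significance level 0.05, power 80%. Follow-up is 1 year. Expected events: 200 × 0.22 = 44.

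**Step 1: the plan's own figure (hypothesis 3a).** For a continuous covariate in a Cox model, events = (z₀.₉₇₅ + z₀.₈₀)² / (SD² × ln(HR)²).
- (1.960 + 0.842)² = 7.85; ln(1.53)² = 0.425² = 0.181; 7.85 / 0.181 = 43.4 events.
- 43.4 / 0.22 ≈ 197 athletes.
- With 44 events, two-sided power is 80.5% and the minimum detectable hazard ratio is 1.526.

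The stated figure reproduces, for 3a only.

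**Step 2: the rule for 3b when neither measure predicts injury.** Simulation set-up: 200 athletes, 22% events, censoring at 1 year, time to stabilization as standard normal noise, and an unadjusted Cox model for each measure. Harrell's c counts predictor ties as 0.5. The clinical score is taken as at ceiling or below it, with an assumed share below. There were 1,500 to 3,000 trials per setting; at 1,500 trials the Monte Carlo standard error near 50% is √(0.25/1500) = 1.3 percentage points.

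Share of trials in which time to stabilization has the higher c, each model choosing its own direction:

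| Athletes below ceiling (assumed) | Time to stabilization declared better |
|---|---|
| 2% | 83% |
| 5% | 76% |
| 10% | 69% |
| 20% | 61% |
| 30% | 57% |
| 50% | 53% |

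Repeat runs gave 72% to 77% with 5% below ceiling, 67% to 70% with 10%, and 61% to 63% with 20%.

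- Mean apparent c is about 0.535 for the noise predictor (97.5th percentile 0.60), against 0.508 to 0.518 for a score with 2% to 10% below ceiling.
- If the score is summed over eight trials (four directions, single and dual task) with 2% to 20% multi-step responses per trial, time to stabilization is declared better in 66% down to 53%.
- If direction is fixed in advance (longer stabilization or lower score means higher risk), it is declared better in 49% to 51% at 95%, 90% and 80% ceiling. Across all fixed-direction null runs, including the summed score, the range is 48% to 53%.

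**Step 3: precision of the difference.** With direction fixed, the SD of the difference in c is 0.047 to 0.058 for the binary score. The 95% half-width is 1.96 × 0.047 = 0.09 to 1.96 × 0.058 = 0.11.

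**Step 4: a rule based on an interval.** Direction was prespecified and a 95% jackknife interval was put on the paired difference in c.
- Neither measure informative: time to stabilization is declared better in 2.5% to 3.1% of trials (2.4% to 3.7% for the summed score).
- Time to stabilization truly at hazard ratio 1.53, score uninformative: the interval favours it in 71%, 66.5% and 60% of trials with 5%, 10% and 20% below ceiling.

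Adjusted models and the bootstrap version of the interval were not simulated.

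**The case against.** A reader might infer that noise will usually beat the clinical score, so that the rule is biased toward the sensor measure. The protocol does not establish that, for three reasons.

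- **Direction.** The excess over 50% arises because each fitted model may choose its own sign, so noise is credited even when slower stabilization goes with less injury. Hypothesis 3a is directional, and a high c in the wrong direction would not support it. With direction fixed, the excess disappears. What remains is a coin flip, which still controls nothing.
- **Ceiling.** The Discussion expects one but gives no percentage. The test is done with eyes closed specifically to make it harder.
- **Score construction.** The article does not say how scores are combined over directions and tasks. One binary score per athlete is the less favourable reading; summing over eight trials brings the figures closer to 50%.

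Nor do the figures show that noise would usually beat a clinical score that is truly predictive. At a hazard ratio of 2 for the score, noise wins 60%, 42% and 24% of trials with 5%, 10% and 20% below ceiling, or 33%, 23% and 13% with direction fixed. That scenario is also strained, because stabilization is timed after the last step and multi-step athletes should tend to take longer.

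A further reading is that the best of three sensor measures competes against one score, from "Similar models will be performed for each secondary outcome". In phase 2 the secondary outcomes could equally be the number and severity of injuries, so nothing here relies on that reading.

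Two general objections remain. Standard errors and validation methods for a c-statistic are commonly left to an analysis plan, and that is fair. The criticism is of the sentence that does fix the decision, not of missing detail. Also, the 3a test at 0.05 would normally expose a useless predictor. This softens the consequence, but 3a is not made a condition for 3b.

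**Conclusion.** The concern holds as a lack of error control. The protocol fixes a rule that declares a winner on the larger of two same-sample c-statistics, although the difference carries a 95% half-width of about 0.09 to 0.11 at the planned size. If neither measure predicts injury, time to stabilization is declared better in about half of trials with direction fixed. With direction left to each model, the figure is about 61% to 77% at an assumed 80% to 95% ceiling, or about 53% to 66% for a score summed over eight trials. The lack of control does not depend on these assumptions; the tilt toward the sensor measure does.

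The scope mismatch is a separate textual point. Beating the one clinical score that is expected to sit at its ceiling would not support a claim about clinical measures in general.

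This is a should-fix point. Hypothesis 3b is a secondary comparison, the phase 2 sample size serves 3a, and the calculation for 3a is correct on its own inputs.

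**What to change.** Replace the highest-c-statistic sentence with a rule of this kind:

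- Estimate the paired difference in c-statistic between time to stabilization and the clinical score in the same athletes.
- Prespecify the direction (longer stabilization or lower score means higher risk), or correct for optimism. An interval alone is not enough if each model may still choose its sign.
- Report a bootstrap 95% CI. Claim 3b only if the lower bound exceeds 0; otherwise report the comparison as descriptive.
- Either run the same comparison against BESS errors and clinical reaction time, or limit the 3b claim to the Push and Release clinical score.

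A likelihood-ratio test of adding time to stabilization to a model that already holds the score is optional. It addresses incremental value, not which measure predicts better.

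The cost is wording and computation, with no new data, and the change should be made before outcomes are analysed. The downside is that 3b becomes harder to declare. Power is about 60% to 71% at a hazard ratio of 1.53 with an uninformative score and 5% to 20% of athletes below ceiling, judged from the jackknife version. The protocol should say so.
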